### 11 SOFTWARE

SAS for Windows, Version 9.4 (SAS Institute, Cary, NC, USA)

R Version 3.6.2

Stata

SPSS 26.0 (SPSS Inc., Chicago, USA)

Table 2. Secondary outcome analyses for comparisons between both groups

| Outcomes                                                                                    | Time of measurement | Refers to...                                 | Scale       | Possible values | Interpretation                                                 | Analysis method             | Analysis population |
|---------------------------------------------------------------------------------------------|---------------------|----------------------------------------------|-------------|-----------------|----------------------------------------------------------------|-----------------------------|---------------------|
| Migraine days per month                                                                     | daily               | week 1-4, week 5-8                           | continuous  | 0-28            | higher values indicate higher disease burden                   | ANCOVA*                     | ITT                 |
| Headache days per month                                                                     | daily               | week 1-4, week 5-8, and week 9-12            | continuous  | 0-28            | higher values indicate higher disease burden                   | ANCOVA*                     | ITT                 |
| Responder rate: at least 30% reduction of migraine days per month compared to baseline      | daily               | week 9-12                                    | dichotomous | Yes, no         | higher values indicate more responders                         | Binary logistic regression* | ITT                 |
| Moderate/severe headache days per month                                                     | daily               | week 1-4, week 5-8, and week 9-12            | continuous  | 0-28            | higher values indicate higher disease burden                   | ANCOVA*                     | ITT                 |
| Days with acute headache medication intake                                                  | daily               | week 1-4, week 5-8, and week 9-12            | continuous  | 0-28            | higher values indicate higher medication use                   | ANCOVA*                     | ITT                 |
| Days with triptans intake                                                                   | daily               | week 1-4, week 5-8, and week 9-12            | continuous  | 0-28            | higher values indicate higher medication use                   | ANCOVA*                     | ITT                 |
| Migraine specific quality of life (HIT-6)                                                   | week 12             | week 9-12                                    | continuous  | 36-78           | higher values indicate lower quality of life                   | ANCOVA*                     | ITT                 |
| Self-efficacy (HMSE-G-SF)                                                                   | week 12             | after 12 weeks                               | continuous  | 6-42            | higher values indicate lower impairment                        | ANCOVA*                     | ITT                 |
| Headache attributed burden (HALT-30)                                                        | week 12             | 30 days                                      | continuous  | ≥0              | higher values indicate higher disease burden                   | ANCOVA*                     | ITT                 |
| Migraine-specific health literacy: item prophylaxis literacy                                | week 12             | after 12 weeks                               | continuous  | 1-4             | higher values indicate lower health literacy                   | ANCOVA*                     | ITT                 |
| Migraine-specific health literacy: disease literacy,                                        | week 12             | after 12 weeks                               | continuous  | 1-4             | higher values indicate lower health literacy                   | ANCOVA*                     | ITT                 |
| Migraine-specific health literacy: trigger literacy                                         | week 12             | after 12 weeks                               | continuous  | 1-4             | higher values indicate lower health literacy                   | ANCOVA*                     | ITT                 |
| Number of patients with concomitant activity/activities against headache (all and specific) | daily               | week 1-4, week 5-8, week 9-12                | dichotomous | Yes, no         |                                                                | Chi             | ITT                 |
| Study dropouts                                                                              |                     | week 1-4, week 5-8, and week 9-12, week 1-12 | dichotomous | Yes, no         |                                                                | Chi             | ITT                 |
| Safety measurements                                                                  |                     |                                              |             |                 |                                                                |                             |                     |
| Counts of serious adverse events                                                            | week 4, 8, and 12   | week 1-4, week 5-8, week 9-12                | continuous  | ≥0              | higher values indicate higher number of serious adverse events | Wilcoxon rank test          | ITT                 |
| Number of patients with at least one serious adverse event                                  | week 4, 8, and 12   | week 1-4, week 5-8, week 9-12                | dichotomous | Yes, no         |                                                                | Chi             | ITT                 |

\* with treatment group (fixed factor) and respective baseline value (if applicable) as covariate

**Table 3.** Descriptive outcomes for the group with M-sense Migräne

| Outcomes                                                        | Time of measurement | Refers to...                  | Scale                                    | Possible values | Interpretation                                                        | Analysis method | Analysis population |
|-----------------------------------------------------------------|---------------------|-------------------------------|------------------------------------------|-----------------|-----------------------------------------------------------------------|-----------------|---------------------|
| Percentage of patients adherend to app use                      | weekly              | weeks 1-12                    | dichotomous                              | Yes, no         | higher percentages indicate better adherence                          | descriptively   | ITT                 |
| Safety measurements                                      |                     |                               |                                          |                 |                                                                       |                 |                     |
| Number of patients with at least one suspected adverse reaction | week 4, 8, and 12   | week 1-4, week 5-8, week 9-12 | dichotomous                              | Yes, no         |                                                                       | descriptively   | Safety population   |
| Duration of suspected adverse reaction                          | week 4, 8, and 12   | week 1-4, week 5-8, week 9-12 | continuous (Minutes, hours, days, weeks) | $\geq 0$        | higher values indicate longer duration                                | descriptively   | Safety population   |
| Counts of suspected adverse reactions                           | week 4, 8, and 12   | week 1-4, week 5-8, week 9-12 | continuous                               | $\geq 0$        | higher values indicate a higher number of suspected adverse reactions | descriptively   | Safety population   |

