## 11.8 Secondary outcomes

Secondary outcomes will be analysed similarly to the primary analysis, i.e. ANCOVA, or logistic or Poisson regression (depending on the scale and distribution of the data), adjusted for sex and the respective baseline value (when available). Detailed description of all analyses will be given in the SAP.

All analyses on secondary outcomes will be considered explorative.

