Based on this explanation we used the following assumptions as basis for the sample size estimation: reduction of migraine days in the intervention group 1.69 migraine days, and in the control group 0.42 migraine days. This resulted in a group difference of 1.27 migraine days in week 9-12 between both groups with a pooled standard deviation of 4.20. Applying a 2-sided T-test for independent groups with a power of 80% and an alpha of 5%, a total of 173 participants will be needed per group (346 participants in total for both arms). Because the primary analyses will follow the intention-to-treat (ITT) principle, all randomized patients will be included and missing data will be imputed, additional patients to compensate for dropouts have not be taken into account. The sample size was calculated with the software PASS 2008 (Version 08.0.16, Release 27.01.2011; Hintze, J. (2008), NCSS, LLC, Kaysville, Utah).

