### 10.5.3 Moderators and Subgroup Analyses

Moderators on the primary outcome will be analyzed by using an analysis of variance (ANOVA) including an interaction term of the moderator and treatment condition. This will provide information on the importance of each moderator on the treatment effect (p-values and explained variance). We will use the following baseline variables as moderators:

- Gender (male/female/other)
- Baseline migraine days (low vs. high based on median split)
- Type of migraine disease (chronic/episodic migraine)
- Duration of migraine disease (short vs. long based on median split)

In addition to that, we will display for each subgroup means and confidence intervals. These analyses will be considered explorative.

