#### 10.5.4 Secondary outcomes

Secondary outcomes, that are considered continuous data, will be analyzed with an ANCOVA similar to the procedure for the primary outcome. A logistic regression analysis or Chi Square Test will be used for the comparison of the two treatment conditions for the dichotomous outcome responder. The analyses of secondary outcomes are summarized in Table 2 and will be considered explorative.

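### Exploratory secondary and moderator models in the SAP leave out covariates that the primary ANCOVA uses, and two continuous moderators are split at the median

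*Combined protocol and SAP*

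**What the plan says.** Randomisation is stratified by episodic versus chronic migraine (protocol 5.4, SAP 3). SAP 3 gives the reason: chronic patients have more migraine days. The primary ANCOVA in SAP 10.5.1 has baseline migraine days and type of migraine as covariates.

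For secondary outcomes there are three descriptions:

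- SAP 10.5.4: continuous outcomes "will be analyzed with an ANCOVA similar to the procedure for the primary outcome". No covariates are listed, and the reader is sent to Table 2.
- SAP Table 2 footnote, attached to every ANCOVA and to the responder logistic regression: "with treatment group (fixed factor) and respective baseline value (if applicable) as covariate".
- Protocol 11.8: "adjusted for sex and the respective baseline value (when available", with the details left to the SAP.

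For the 30% responder outcome, SAP 10.5.4 permits either logistic regression or a chi-square test, while Table 2 lists logistic regression only.

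Under SAP 10.5.3, moderators "will be analyzed by using an analysis of variance (ANOVA) including an interaction term" of moderator and treatment. No covariates are named. The four moderators are gender, type of migraine, disease duration split at its median, and "Baseline migraine days (low vs. high based on median split".

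**The concern.** The sponsor judged type of migraine prognostic enough to stratify on it and to put it in the primary model, yet the only explicit covariate list for secondary outcomes in the SAP leaves it out. A stratification factor that predicts outcome should be in the analysis model. Otherwise the standard errors do not reflect the balance that the design achieved and come out somewhat too wide. The conflict with 10.5.4 also leaves the analyst to choose the model.

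The moderator analyses are meant to show how important each moderator is, through p-values and explained variance. Interaction tests have low power to begin with. Leaving out a strong predictor of outcome and splitting continuous moderators weakens them further, so a finding of no moderation would say little. Protocol Table 2 maps several secondary outcomes to benefit categories under the Digital Healthcare Act, so their precision has practical value although they are exploratory.

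**Working it through.** **1. The plan's own figure.** SAP 7 is "Applying a 2-sided T-test for independent groups" at two-sided alpha 0.05 and 80% power, with a "group difference of 1.27 migraine days in week 9-12" (1.69 - 0.42) and SD 4.20. The normal approximation is n = 2 × (1.960 + 0.842)² × 4.20² / 1.27² = 171.7, so 172 per group. The exact t-test gives 173 (power 0.8008 at 173, 0.7985 at 172). The stated 173 reproduces. It comes from an unadjusted test, so nothing below changes it.

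**2. Stratum added to a secondary ANCOVA that already has its own baseline.** If the stratum has partial correlation p with outcome given baseline, the standard error is multiplied by √(1 - p²). For assumed p = 0.05, 0.1, 0.2 and 0.3 the reduction is 0.1%, 0.5%, 2.0% and 4.6%.

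A simulation of a migraine-day outcome agrees. It used N = 346 with stratified 1:1 allocation and 2,000 runs per scenario. Assumptions: 10-30% chronic, 8 days' baseline difference between strata, within-stratum baseline SD 3.5, slope 0.6, residual SD 3.7, stratum effect beyond baseline 0, 1 or 3 days, treatment effect 1.27. The standard error was 0.397-0.411 with baseline only and 0.398 with the stratum added. Power changed by about 2 points at most.

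**3. Which moderator models contain what.**

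| Moderator | Baseline migraine days in model? | Stratum in model? |
|---|---|---|
| Gender | no | no |
| Disease duration (split) | no | no |
| Type of migraine | no | yes |
| Baseline migraine days (split) | dichotomised only | no |

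**4. Baseline left out altogether.** Take a 50/50 moderator, 346/4 = 86.5 patients per cell and SD 4.20. The interaction standard error is 4.20 × √(4/86.5) = 0.903. Adjusting for baseline with baseline-outcome correlation r multiplies it by √(1 - r²). The interaction detectable with 80% power is 2.80 times the standard error.

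| Assumed r | SE unadjusted | SE adjusted | Inflation 1/√(1 - r²) | Detectable interaction (days), unadjusted to adjusted |
|---|---|---|---|---|
| 0.3 | 0.903 | 0.862 | 1.05 | 2.53 to 2.41 |
| 0.5 | 0.903 | 0.782 | 1.15 | 2.53 to 2.19 |
| 0.7 | 0.903 | 0.645 | 1.40 | 2.53 to 1.81 |

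Unadjusted, the detectable interaction is about twice the planned treatment effect (2.53/1.27 = 1.99).

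**5. Baseline present only as a median split.** For a normal variable, the squared correlation with its median split is 2/π = 0.637. The standard error relative to full adjustment is √[(1 - 0.637r²)/(1 - r²)]. At r = 0.5 this is √(0.841/0.75) = 1.06, and at r = 0.7 it is √(0.688/0.51) = 1.16.

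**6. Splitting the moderator itself.** With a normal moderator and a linear interaction, the split keeps 2/π = 64% of the information. A test with 80% power in continuous form falls to Φ(2.80 × √0.637 - 1.96) = 0.61.

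**The case against.** The strongest answer is that nothing confirmatory is touched. Only the primary test is confirmatory (SAP 9.1), its model already has both covariates, and the secondary and moderator analyses are declared exploratory. Omitting a prognostic covariate from these linear models costs precision but does not bias the randomised comparison. Median splits are a common exploratory display. All of this stands, and it limits the weight of the point. It does not remove the gain from using data already collected.

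Several stronger readings are tempting, but the documents do not support them:

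- A reader might infer that every moderator model lacks baseline and stratum and uses a split. Only the gender and duration models lack both variables, and only two of the four moderators are split.
- A reader might apply the 15-40% inflation to all moderator models. In the baseline-split model it is about 6-16% over the same correlations. In the type-of-migraine model the stratum carries some baseline information.
- A reader might conclude that the responder regression is unadjusted. The footnote applies to it, and since response is defined against baseline migraine days, that variable could be the baseline value meant. The text is ambiguous. Moreover, adding covariates to a logistic model changes the odds ratio being estimated and need not shrink its standard error, so the argument here is mainly one of fixing the model in advance.
- A reader might count three competing secondary models. Protocol 11.8 defers to the SAP, and SAP 1 and 5 say the SAP replaces the evaluation concept, so the sex adjustment is superseded. The live conflict is within the SAP, between 10.5.4 and the Table 2 footnote. Reading 10.5.4 as carrying over the stratum does not settle it, because 10.5.4 itself points to Table 2.

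**Conclusion.** The point holds as an inexpensive improvement to exploratory analyses. The Table 2 footnote omits the randomisation stratum and conflicts with SAP 10.5.4. The responder model is not fully specified. The moderator ANOVA names no covariates and dichotomises two continuous variables. The primary test and the 173 per group are unaffected.

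The losses are uneven. For secondary ANCOVAs the stratum is worth about 0-5% of the standard error once own baseline is in the model. The larger losses are in the moderator models: about 5%, 15% and 40% on the interaction standard error at r = 0.3, 0.5 and 0.7 where no baseline information is present, about 6% and 16% at r = 0.5 and 0.7 where baseline is split, and about 36% of the information for a split moderator.

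All these sizes are conditional. The documents give no baseline-outcome correlation, chronic share or stratum effect. The 64% figure needs normality and a linear interaction, whereas entry requires at least 3 baseline migraine days, so the true figure could be higher or lower.

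**What to change.** - **Table 2 footnote:** list treatment group, the outcome's own baseline value where one exists, and type of migraine (episodic/chronic). State the same set in SAP 10.5.4, and align protocol 11.8 with it.
- **Responder outcome:** specify logistic regression with treatment, baseline migraine days and type of migraine, and delete the chi-square alternative from SAP 10.5.4.
- **SAP 10.5.3:** fit the primary ANCOVA plus the moderator (where it is not already a covariate) and its interaction with treatment. Keep baseline migraine days and disease duration continuous in the test, and use median-split means and intervals for display only.

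The cost is SAP and protocol wording. Every variable is already collected, and no patient, visit or sample-size change is needed.
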